**Fig. 4 Fig4:**
[figure not shown]
Developmental stages of Anopheline ovaries [31]. Mosquitoes with fully developed stage V ovaries (elongated boat-shaped eggs with lateral floats) are considered fertile while mosquitoes with stage I-IV ovaries containing underdeveloped eggs are considered infertile

All bioassays will be performed at 27 ± 2 °C and 75% ± 10% relative humidity. For each ITN type, each active ingredient and each bioassay, a direct comparison will be made with a new unused net during bioassays. A new Interceptor^®^ net will be tested as positive control in bioassays evaluating pyriproxyfen in Royal Guard^®^ and chlorfenapyr in Interceptor^®^ G2. Prior to each bioassay round, susceptibility tests will be performed to monitor the suitability of the *An coluzzii* Akron strain. While efforts will be made to test nets withdrawn at all timepoints (every 6 months) in laboratory bioassays, given the volume of bioassays required, to improve efficiency, nets withdrawn at 0, 6, 12, 24 and 36 months post-ITN distribution will be prioritized over other timepoints.

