## Methods

### Study arms

The study consists of three arms evaluating the durability of two dual AI ITNs (Interceptor^®^ G2 and Royal Guard^®^) compared to a standard pyrethroid-only ITN Interceptor^®^. Study nets are all blue, rectangular, and sizes of 1.8 m long, 1.8 m wide, and 1.8 m high (Interceptor^®^ and Interceptor^®^ G2) and 1.8 m long, 1.8 m wide, and 1.6 m high (Royal Guard^®^). A description of the specifications of the three ITN types is provided below:Interceptor^®^ G2 (BASF AGRO B.V.), is a WHO-prequalified 100-denier, polyester ITN coated with a mixture of alpha-cypermethrin and chlorfenapyr at target concentrations of 100 mg/m^2^ (± 25%) and 200 mg/m^2^ (± 25%), respectively. The bursting strength of the fabric is ≥ 405 kPa while the mass per unit area is 40 g/m^2^ (± 10%) for 100 denier yarn.Royal Guard^®^ (Disease Control Technologies, LLC, USA), is a WHO-prequalified 100-denier, polyethylene ITN incorporated with a mixture of alpha-cypermethrin and pyriproxyfen at target concentrations of 261 mg/m^2^ (± 25%) and 225 mg/m^2^ (± 25%) respectively. The bursting strength of the fabric is ≥ 405 kPa while the mass per unit area is 45 g/m^2^ (± 10%) for 150 denier yarn.Interceptor^®^ (BASF AGRO B.V.), is a WHO-prequalified 100-denier, polyester ITN coated with alpha-cypermethrin at target concentrations of 200 mg/m^2^ (± 25%). The bursting strength of the fabric is ≥ 405 kPa while the mass per unit area is 40 g/m^2^ (± 10%) for 100 denier yarn. Interceptor® is the control arm of the trial against which Interceptor^®^ G2 and Royal Guard® are compared.

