#### Laboratory bioassays and strain selection

Cone bioassays and tunnel tests will be performed at the CREC-LSHTM GLP-certified facility to monitor the bioefficacy of each active ingredient in each ITN brand using ITN pieces obtained from field collected nets at each time point. Current WHO ITN durability guidelines were tailored towards pyrethroid-only nets and therefore do not describe methods for assessing the bioefficacy of non-pyrethroid chemicals on ITNs [13]. Unlike pyrethroids that require a pyrethroid-susceptible *Anopheles* strain for durability bioassays, evaluation of the insecticidal activity of chlorfenapyr in Interceptor^®^ G2 and pyriproxyfen in Royal Guard® will require the use of a pyrethroid-resistant strains that is susceptible to these insecticides to reduce any confounding effects from the pyrethroid component.

Following a series of preliminary laboratory bioassays, the pyrethroid resistant *An. coluzzii* Akron strain (BEI resources) maintained at the CREC-LSHTM insectary since 2018 was identified as a suitable strain for monitoring the bioefficacy of chlorfenapyr and pyriproxyfen in Interceptor^®^ G2 and Royal Guard^®^ ITNs from the trial. Preliminary WHO susceptibility bottle bioassays [28, 29] performed with alpha-cypermethrin (12.5μg), chlorfenapyr (100μg) and pyriproxyfen (100μg) showed that the strain was resistant to pyrethroids but susceptible to chlorfenapyr and pyriproxyfen (Fig. 3). Mortality with deltamethrin in WHO tube assays increased from 19 to 77% demonstrating the partial involvement of mixed function oxidases in pyrethroid resistance in the Akron strain. Dissection of ovaries of blood-fed *An. coluzzii* Akron mosquitoes exposed to pyriproxyfen treated bottles revealed a 98% reduction in mosquito fertility relative to unexposed mosquitoes thus showing susceptibility to pyriproxyfen. The WHO cone bioassays performed with Akron mosquitoes using unwashed and washed pieces of the pyrethroid-only ITN (Interceptor^®^) showed high survival (> 60%) demonstrating that the impact of chlorfenapyr and pyriproxyfen in Interceptor^®^ G2 and Royal Guard^®^ will be less confounded by the alphacypermethrin component in these nets when tested in laboratory bioassays using this strain.

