**Fig. 3 Fig3:**
[figure not shown]
Susceptibility of the pyrethroid-resistant *Anopheles coluzzii* Akron strain to insecticides in study nets. Chlorfenapyr, pyriproxyfen and alpha-cypermethrin exposures were performed in WHO bottle bioassays while deltamethrin exposures were performed in WHO filter paper tube tests. Approximately 100 mosquitoes of each strain were exposed for 1 h to each insecticide in replicates of 25. For pyriproxyfen, mosquitoes were blood-fed before exposure and their ovaries dissected after 72 h to assess ovary development

Based on results from these preliminary bioassays, the testing plan in Table 2 will be used in laboratory bioassays for monitoring the bioefficacy of each active ingredient in the different ITN brands in the trial. In line with WHO guidelines, ITN bioefficacy at each timepoint will be expressed in terms of the proportion of ITNs passing the efficacy criteria for each active ingredient in cone bioassays or tunnel tests.

**Table 2 Tab2:** Summary of laboratory bioassay methodology and outcome measures for assessing the insecticidal durability of Interceptor^®^ G2 and Royal Guard^®^ in Benin compared to Interceptor^®^

ITN type	Brand name	Active ingredient	Mosquito strain	Mosquito age and status (N)	Primary test method (exposure time)	Key outcome measures	ITN efficacy criteria	Remarks/additional tests
Pyrethroid-only	Interceptor	alpha-cypermethrin	Susceptible *An. gambiae* s.s. Kisumu	unfed, 3–5 days old (40–50/net)	cone bioassays (3 min)	Knockdown, 24 h Mortality	knock-down ≥ 95% or mortality ≥ 80%	Tunnels for failed nets
Pyrethroid-chlorfenapyr	Interceptor G2^a^	alpha-cypermethrin	not tested	not tested	not tested	not tested	not tested	not tested due to lower dose of pyrethroid
		chlorfenapyr	Pyrethroid-resistant *An. coluzzii* Akron	unfed, 5–8 days old (100/net)	Tunnel tests (overnight)	72 h Mortality and Blood-feeding inhibition	Mortality ≥ 80% or Blood-feeding inhibition ≥ 80%	1 net piece per ITN
Pyrethroid- pyriproxyfen	Royal Guard	alpha-cypermethrin	Susceptible *An. gambiae* s.s. Kisumu	unfed, 5–8 days old (40–50/net)	cone bioassays (3 min)	Knockdown, Mortality	knock-down ≥ 95% or mortality ≥ 80%	Tunnels for failed nets
		pyriproxyfen	Pyrethroid-resistant *An. coluzzii* Akron	blood-fed, 5–8 days old (80–100/net)	cone bioassays (3 min) plus ovary dissection after 72 h	% reduction in fertility relative to control^b^	Reduction in fertility relative control	> 30% fertility required in control

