^a^For Interceptor G2, given the low dose of alpha-cypermethrin, chlorfenapyr bioefficacy will be prioritised

^b^Mosquitoes presenting with Christopher stage V ovaries, will be considered fertile

Alpha-cypermethrin bioefficacy in Royal Guard^®^ and Interceptor^®^ will be assessed using the susceptible *An. gambiae* Kisumu strain in 3 min cone bioassays following current WHO protocols. At each timepoint, 40–50 unfed 3–5 days old *An. gambiae* Kisumu mosquitoes will be exposed to each whole Royal Guard^®^ and Interceptor^®^ ITN in replicates of 5 mosquitoes per cone and 2 cones per ITN piece. ITNs which fail to achieve WHO efficacy criteria in these cone bioassays (pooled knock-down ≥ 95% or pooled 24h mortality ≥ 80%) will be subjected to tunnel tests. For each ITN that failed in cone bioassays, only one ITN piece (with cone bioassay mortality that is closest to the mean) will be tested in tunnels. Approximately 100 unfed 5–8 days old susceptible *An gambiae* Kisumu will be exposed to each ITN piece in the tunnel tests and efficacy of alpha-cypermethrin in Interceptor^®^ and Royal Guard^®^ will be measured in terms of mortality after 24h (≥ 80%) or blood-feeding inhibition (≥ 90%).

Given the relatively low concentration of alpha-cypermethrin in Interceptor^®^ G2 (100 mg/m^2^), bioefficacy studies performed with the net will focus more on its chlorfenapyr component. The unsuitability of cone bioassays for assessing the efficacy of chlorfenapyr on ITNs has been demonstrated in several studies [19, 30] hence only tunnel tests will be used for evaluating the activity of chlorfenapyr in Interceptor^®^ G2 with the pyrethroid-resistant Akron strain. To improve the efficiency of the tunnel test bioassays, only 1 ITN piece per whole Interceptor^®^ G2 will be tested in tunnels. A total of ~ 100 unfed 5–8 days old pyrethroid resistant *An coluzzii* Akron will be exposed overnight in each tunnel test with Interceptor^®^ G2 and efficacy in tunnels will be measured in terms of mosquito mortality after 72h (≥ 80%) or blood-feeding inhibition (≥ 90%).

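### After month 0 no laboratory test holds both field-aged Interceptor G2 and field-aged Interceptor, so their pass rates cannot be compared, and passes on blood-feeding inhibition alone are weakly attributable to chlorfenapyr

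*Protocol article*

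**What the plan says.** The second study objective is to examine the insecticidal activity and chemical content of Interceptor G2 and Royal Guard against Interceptor over three years.

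The section on laboratory bioassays and strain selection, with Table 2, assigns the tests:

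- **Interceptor and Royal Guard, alpha-cypermethrin.** Both are tested with the susceptible "Kisumu strain in 3 min cone bioassays following current WHO protocols". Nets that fail go to tunnels with the same strain: about 100 "Kisumu will be exposed to each ITN piece in the tunnel tests and efficacy of alpha-cypermethrin in Interceptor" and Royal Guard is read as 24 h mortality or blood-feeding inhibition.
- **Interceptor G2, chlorfenapyr.** Cones are judged unsuitable, "hence only tunnel tests will be used for evaluating the activity of chlorfenapyr in Interceptor" G2. The strain is the resistant Akron, and a net passes on 72 h mortality or on blood-feeding inhibition.
- **Interceptor G2, alpha-cypermethrin.** Table 2 records it as "not tested due to lower dose of pyrethroid".

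The control arrangements follow Fig. 4. Each net type, active ingredient and bioassay gets a direct comparison with a new unused net. In addition, a new Interceptor "net will be tested as positive control in bioassays evaluating pyriproxyfen in Royal Guard" and chlorfenapyr in Interceptor G2.

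Akron was chosen after preliminary work in which cone tests on unwashed and washed Interceptor "showed high survival (> 60"%). The article concludes that pyrethroid confounding will be reduced; it does not claim that it is absent.

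Under Study arms, Interceptor is "coated with alpha-cypermethrin at target concentrations of 200 mg/m^2" and Interceptor G2 is "coated with a mixture of alpha-cypermethrin and chlorfenapyr at target concentrations of 100 mg/m^2" for its pyrethroid. The Statistical analysis section plans a chi-squared test on the proportion of nets of each type that pass, combining cone and tunnel results.

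**The concern.** The objective is comparative, but the laboratory schedule gives the two aged nets no test in common. A difference in pass rate between Interceptor G2 and Interceptor would mix a strain difference, an assay difference, a reading-time difference and a difference in active ingredient with whatever difference in activity exists.

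The second question is attribution. A field Interceptor G2 net that passes is counted as having active chlorfenapyr. The net-based evidence that pyrethroid has limited effect on Akron comes from 3-minute cones, whereas the test used is an overnight tunnel. The Discussion itself treats these as different exposures. The pass rule also accepts blood-feeding inhibition alone, and the article gives no Akron blood-feeding result for any pyrethroid-only net, new or aged.

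What is at stake is the article's stated purpose of showing whether the costlier non-pyrethroid component lasts, and of identifying methods suited to monitoring it.

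**Working it through.** There is no stated figure to reproduce. The check sets the assays side by side and then asks how easily pyrethroid alone could produce a pass.

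**Step 1. Which nets share a test** (Table 2, the text below it, and the control paragraph after Fig. 4)

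| Net | Kisumu cone | Kisumu tunnel (24 h) | Akron tunnel (72 h) | Akron cone with dissection |
|---|---|---|---|---|
| Field Interceptor | yes | if failed | no | no |
| Field Royal Guard | yes | if failed | no | yes |
| Field Interceptor G2 | no | no | yes | no |
| New Interceptor | yes | not stated | yes | yes |

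No column holds both field Interceptor and field Interceptor G2. Field Royal Guard and field Interceptor share the Kisumu columns, so the gap concerns Interceptor G2 only. At month 0 all sampled nets are new, so the new Interceptor in the Akron tunnels is a same-age comparator there. The gap opens at the first field round.

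The chi-squared sentence names no contrasts. Read by active ingredient, chlorfenapyr has one net type and no partner. Read by net type, it pairs mismatched assays. Neither reading gives a laboratory comparison of activity between these two nets.

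**Step 2. Mortality route**

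Inputs: about 100 mosquitoes per tunnel; cut-off 80%; survival above 60% in cones, hence mortality below 100% − 60% = 40%. The tunnel figure is not given, so it is varied. Deaths are taken as Binomial(100, m), and the result is P(at least 80 deaths).

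| Pyrethroid-only mortality m | P(pass) |
|---|---|
| 40% | 3 × 10^-16 |
| 60% | 2 × 10^-5 |
| 70% | 0.016 |
| 75% | 0.15 |
| 80% | 0.56 |

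Tunnel mortality would have to be far above the cone ceiling before pyrethroid alone passed nets with any frequency.

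**Step 3. Blood-feeding-inhibition route**

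Assumptions: 100 mosquitoes, control feeding c = 70% treated as known, true pyrethroid-only inhibition b. The expected fed proportion is c(1 − b). A net passes at cut-off t if the number fed is at most 100 × c × (1 − t), which is 14 for t = 80% and 7 for t = 90%.

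| True inhibition b | P(pass), 80% cut-off (Table 2) | P(pass), 90% cut-off (text) |
|---|---|---|
| 70% | 0.05 | 0.0001 |
| 80% | 0.57 | 0.02 |
| 85% | 0.90 | 0.16 |

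The article gives no value of b, so the table shows sensitivity and is not an estimate. At a true inhibition of 80% to 85%, the answer turns largely on which of the two stated cut-offs applies.

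**Step 4. Material available**

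Table 1 cuts 4 pieces from each field net: 30 × 4 = 120 pieces per net type at 12 and at 24 months, and 50 × 4 = 200 at 36 months. For Interceptor, at most one piece per net goes on to a Kisumu tunnel, and only when the net failed in cones.

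**The case against.** The other side has real strength. The new Interceptor has twice the target pyrethroid dose of Interceptor G2 (200 against 100 mg/m²) and has not aged. It is therefore a conservative reference: if it fails in the Akron tunnel, a pass by an aged Interceptor G2 is not plausibly due to pyrethroid. That stands. A reader might infer that a chlorfenapyr pass can never be told from a pyrethroid pass, or, from 40/80, that half the kill of a net at the 80% cut-off could be pyrethroid. The documents do not support either as a flaw in the endpoint, which is pass or fail: a net with only 40% pyrethroid mortality would fail on mortality.

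A reader might also infer that objective 2 cannot be met for Interceptor G2. That goes too far. Hut trials test 54 field nets of each type side by side at 12, 24 and 36 months, and chemical content is measured on pieces adjacent to the bioassay pieces at 0, 12, 24 and 36 months.

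The choice of assay is also deliberate and argued from mode of action, and the Discussion admits the limits of the cut-offs. A same-age Interceptor also began at double the dose, so it is not a perfect comparator.

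What these points leave untouched is narrower. The conservative reference helps only while it fails; if it passes on blood-feeding inhibition, it cannot settle the cause. Chemical content is not activity. At 6, 18 and 30 months there is neither a hut trial nor a chemical analysis. Nothing in the objection makes the two laboratory pass rates comparable.

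**Conclusion.** The point holds in limited form. After month 0 the laboratory bioassays give no like-for-like comparison of Interceptor G2 with Interceptor, and a chi-squared test between their pass rates would not measure relative activity. Royal Guard is not affected in this way, and the annual hut trials remain a valid comparison of aged nets.

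Attribution to chlorfenapyr is sound for mortality passes if tunnel mortality from pyrethroid is anywhere near the cone ceiling. It is weakest for nets that pass on blood-feeding inhibition alone. How many nets that concerns cannot be computed, because neither Akron feeding inhibition on a pyrethroid-only net nor the share of such passes is given. The probabilities above assume independent mosquitoes within a tunnel and, for feeding, 70% control feeding; variation between tunnels would widen the tails.

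Two wording matters add to it. The new Interceptor is called a positive control although it contains neither chlorfenapyr nor pyriproxyfen. The inhibition cut-off for Interceptor G2 is 80% in Table 2 and 90% in the text below it.

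**What to change.** 1. In the Akron tunnel rounds with aged nets, at least at 12, 24 and 36 months, run already-cut pieces from same-age field Interceptor nets as a pyrethroid-only comparator in some batches. Keep the new Interceptor in every round as a fixed reference.
2. Report 72 h mortality and blood-feeding inhibition separately for Interceptor G2 and same-age Interceptor, noting that their starting pyrethroid doses differ.
3. State that Interceptor G2 pass rates in Akron tunnels will not be tested against Interceptor pass rates on Kisumu.
4. Call Interceptor the pyrethroid-only comparator in these assays, and new Interceptor G2 the positive control for chlorfenapyr.
5. Reconcile the blood-feeding-inhibition cut-off for Interceptor G2 between Table 2 and the text.

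Swapping the comparator in some batches needs no extra tunnels and no extra nets. The cost is fewer repeats of the new-Interceptor reference. By the article's status section, bioassays on nets up to 24 months were still under way, so at least the 36-month round could be arranged this way. Items 2 to 5 are changes of wording and analysis only.

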### Chemical analysis

Net pieces preserved for chemical analysis at 0, 12, 24 and 36 months (590 pieces per net type) will be wrapped in Aluminium foil and stored at 4^°^c (± 2°c) and afterwards shipped to Centre Walloon de Recherches Agronomiques (CRA-W), Belgium, for detection of fabric weight and active ingredient content. The methods to be used for AI extraction have been described elsewhere [30]. Gas Chromatography with Flame Ionisation Detection (GC-FID) will be used to determine the content of each AI. ITN pieces from the same net will be pooled to provide a single chemical content reading per AI for each whole ITN per net type sampled at each time point.

### Experimental hut trials to assess insecticidal durability

To further assess the entomological superiority of Interceptor^®^ G2 and Royal Guard^®^ over Interceptor^®^, experimental hut trials will be performed with field collected ITNs at 12-, 24- and 36-months post ITN distribution at the Cove experimental hut station against wild free-flying pyrethroid-resistant *An. gambiae *sensu lato (*s.l*.). The Cove experimental hut station is situated in a large rice-growing field within the study area of the cRCT. The vector population at Cove exhibits intense resistance to pyrethroids [32], but is susceptible to chlorfenapyr and pyriproxyfen [30]. To provide some comparison to pyrethroid-PBO nets, PermaNet^®^ 3.0 nets (a WHO prequalified deltamethrin plus PBO ITN by Vestergaard Sarl) that were distributed by the NMCP in the Didja district (7^°^20’N 1^°^56’E) of the Zou Department, a neighbouring community to the cRCT study area, at the same time as the cRCT will also be marked at baseline and withdrawn at each annual timepoint and assessed in the experimental hut trials alongside Interceptor^®^ G2 and Royal Guard®. Three sets of hut trials will be performed: one with 12 months old field nets, the second with 24 months old field nets and the third with 36 months old field nets. Fifty-four (54) field nets of each brand will be tested in the huts at each annual timepoint for a total of 54 nights with each field net spending only 1 night in the experimental huts. Comparison will be made with new unused nets of each type. Six replicates of unused nets of each ITN type will also be tested, and each net will be given six 4 × 4cm holes prior to the trial, following WHO procedures. The hut trials will consist of the following 9 treatments:Untreated net—6 replicatesInterceptor^®^ (new unused)—6 replicatesPermaNet^®^ 3.0 (new unused)—6 replicatesRoyal Guard^®^ Benin (new unused)—6 replicatesInterceptor^®^ G2 (new unused)—6 replicatesInterceptor^®^ field net (12/24/36-months)—54 replicatesPermaNet^®^ 3.0 field net (12/24/36-months)—54 replicatesRoyal Guard^®^ field net (12/24/36-months)—54 replicatesInterceptor^®^ G2 field net (12/24/36-months)—54 replicates

Each hut trial will last 9 weeks and will involve 9 consenting human volunteers sleeping in huts from dusk to dawn 6 days of each week of the trial. Treatments will be rotated each week using a randomized Latin Square Design to control for bias due to hut position and to minimize carry over effects between treatments. Sleepers will be rotated daily to control sleeper attractiveness to mosquitoes. On the 7th day of each week, huts will be cleaned and aired in preparation for the next rotation cycle. The trials will run for a total of 54 nights and replicate nets collected from the field will be rotated between huts on successive nights (one net per night). Nets will be made available for laboratory bioassays and chemical analysis as described earlier, immediately after they have been tested in experimental huts.

The efficacy of each ITN hut treatment at each timepoint will be measured in terms of the following outcome measures:Percentage reduction in mosquito entry relative to the control (deterrence)Percentage of mosquitoes dead after 72 h,Percentage of mosquitoes exiting into the veranda trapPercentage reduction in mosquito blood-feeding relative to the control untreated netsPercentage reduction in proportion of fertile surviving blood-fed mosquitoes after dissection relative to surviving blood-fed mosquitoes in the untreated control hut

WHO susceptibility bioassays will be performed to assess the susceptibility of the wild vector population at the Cove experimental hut station to the insecticides in the study nets during each hut trial.

### Experimental hut trials to compare 36 months old naturally aged field nets to washed nets

To investigate the capacity of ITN washing (20 times) to predict the performance of field aged ITNs, we will conduct another hut trial comparing nets of each ITN type washed 20 times to 36 months naturally aged field nets. ITN washing will follow WHO protocols for hut trials [13]. A total of 78 replicate 36 months old naturally aged field-collected nets of each ITN type will be tested over 78 nights. Six replicates of unwashed and washed nets of each ITN type will be tested, and each net will be given six 4 × 4cm holes following WHO guidelines. The hut trial will also be performed at the Côvè experimental hut station and will consist of the following 13 hut treatments.Untreated net—6 replicatesInterceptor^®^ (new unused)—6 replicatesPermaNet^®^ 3.0 (new unused)—6 replicatesRoyal Guard^®^ Benin (new unused)—6 replicatesInterceptor^®^ G2 (new unused)—6 replicatesInterceptor^®^ (washed 20 times)—6 replicatesPermaNet^®^ 3.0 (washed 20 times)—6 replicatesRoyal Guard^®^ Benin (washed 20 times)—6 replicatesInterceptor^®^ G2 (washed 20 times)—6 replicatesInterceptor^®^ (36-months field net)—78 replicatesPermaNet^®^ 3.0 (36-months field net)—78 replicatesRoyal Guard^®^ (36-months field net)—78 replicatesInterceptor^®^ G2 (36-months field net)—78 replicates

The trial will run for 13 weeks and will involve 13 consenting human volunteers sleeping in huts from dusk to dawn 6 days of each week of the trial. As with the other hut trials, treatments will be rotated each week using a randomized Latin Square Design and sleepers rotated daily and huts cleaned and aired on the 7th day of each week in preparation for the next rotation cycle. The trial will run for a total of 78 nights and the replicate 36 months old naturally aged field nets will be rotated between huts on successive nights (one net per night). Efficacy will be measured in terms of mosquito deterrence, mortality (72h), exiting, blood-feeding inhibition, reduction in fertility of blood-fed survivors as described earlier.

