### Bioefficacy studies and chemical analysis with cohort 2 nets

Nets belonging to cohort 2 will be randomly selected per arm for bioefficacy studies and chemical analysis. Nets of each type (Interceptor^®^ G2, Royal Guard^®^ and Interceptor^®^) will be destructively sampled from households at 6, 12, 18-, 24-, 30- and 36-months post-distribution and replaced with new nets of the same type at each sampling point. They will be subjected to laboratory bioassays (WHO cone bioassays and tunnel tests where necessary) and experimental hut trials to monitor entomological efficacy against mosquito vectors and to chemical analysis to monitor changes alphacypermethrin, chlorfenapyr and pyriproxyfen content. For laboratory bioassays, net pieces measuring 30cmx30cm will be cut from each net following WHO guidelines [13]. Nets withdrawn at annual time points (12, 24 and 36 months) will be tested in experimental huts before laboratory bioassays. The number of whole ITNs of each type to be subjected to each type of study at each timepoint is summarized in Table 1 below.

**Table 1 Tab1:** Number of Interceptor^®^ G2, Royal Guard^®^ and Interceptor^®^ ITNs to be sampled from Cohort 2 at each timepoint

Months post ITN distribution	No of ITNs to withdrawn for bioefficacy studies	No. of ITN to test in hut trials	No. of ITNs to test in lab bioassays	No. of pieces per ITN	Total number of pieces for bioassays	No. of pieces for chemical analysis^b^	ITNs sampled for other studies^c^	
0	30	–	30	5	150	150		
6	30	–	30	4	120	–		
12	54^a^	54^a^	30	4	120	120	80	
18	30	-	30	4	120	-		
24	54^a^	54^a^	30	4	120	120	80	
30	30	–	30	4	120	–		
36	54^a^	54^a^	50	4	200	200	80	
Total	282				950	590	240	

^a^These nets will be tested in hut trials prior to laboratory bioassays and chemical analysis. Hut trials will only be performed with nets withdrawn at 12, 24 and 36 months

^b^Net pieces preserved for chemical analysis will be obtained from adjacent positions on the same ITNs cut for bioassays

^c^These nets will be samples from cohort 2 nets but will be used in other studies

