### Sample size calculations

Sample size calculations are performed based on previous ITN durability data from Benin. For cohort 1, a sample size of 750 nets of each brand from 250 randomly selected households (assuming ~ 3 ITNs are distributed per household) in 5 study clusters was found sufficient to detect a 9.4% absolute difference (hazard ratio = 0.87) in ITN attrition rate assuming an attrition rate in the control arm of 70% over the 3 years and an intra-cluster correlation coefficient of 0.03. For cohort 2, a total of 522 ITNs will need to be withdrawn over three years and assuming a loss rate of 70% a total of 1800 ITNs will be marked per study arm at baseline. To reduce the impact of the durability study on the outcomes of the cRCT, cohort 2 nets will be obtained from households in the buffer areas of the selected clusters to exclude the core areas used for the cRCT sampling.

For each experimental hut trial and at each timepoint, data on the number of mosquitoes per night and the magnitude of the different random effects (huts, sleepers, nights and observational error) will be reviewed after the first round of 9 or 13 weeks and power calculations conducted by simulation using previously described methods [33]. Power analysis will determine whether the hut trial has a desired 80% power to detect superiority in mosquito killing of any new unused dual AI ITN over the new unused pyrethroid-only net, assuming a true underlying extra mortality from the dual AI net of 40%. A second round of hut trial would be performed if the desired level of power is not achieved.

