### Statistical analysis

Data from the surveys at 6, 12, 24, and 36 months will be used to calculate attrition, functional survival and median survival time using Kaplan–Meier estimators. For functional survival, nets reported as given away, sold, or stolen will be excluded from the analysis. Negative binomial regression will be used to compare hole surface area between the different ITN types. Data on WHO cone bioassays and tunnel tests will be obtained from 30 nets of each product type sampled at each time point. A chi-squared test will be used to assess the proportion of nets of each ITN type passing the WHO criteria for alphacypermethrin, chlorfenapyr and pyriproxyfen bioefficacy based on combined cone and tunnel tests. Proportional outcomes (mortality, blood-feeding, exophily) from the experimental hut trials will be compared at each time point using mixed effects logistic regression, with huts, sleepers, net replicate and nightly observational error included as random or fixed effects [33]. Numerical outcomes (hut entry) will be compared using negative binomial regression. A separate model will be fitted for each outcome to determine whether there is (i) a significant change over time, and (ii) a significant difference between ITNs washed 20 times and 36-month-old naturally aged ITNs. Analysis will be performed on STATA or the package *lme4* of the R software.

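### Table 1 and the 522-net withdrawal total leave out the 78 field nets per type, aged 36 months, that the washed-versus-aged hut trial requires

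*Protocol article*

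**What the plan says.** The protocol article describes two hut experiments that use field nets aged 36 months.

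- **Annual trial** (section on hut trials to assess insecticidal durability): "Fifty-four (54) field nets of each brand will be tested in the huts at each annual timepoint for a total of 54 nights". Each of these nets is used for a single night. The trial has nine treatments and is run at 12, 24 and 36 months.
- **Washed-versus-aged trial** (section comparing 36-month field nets with washed nets): "we will conduct another hut trial comparing nets of each ITN type washed 20 times to 36 months naturally aged field nets". It has 13 treatments, and "A total of 78 replicate 36 months old naturally aged field-collected nets of each ITN type will be tested over 78 nights", with one field net of each type per night.

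Table 1, in the section on bioefficacy studies with cohort 2 nets, gives the number of nets taken from cohort 2 at each time point. Its 36-month row has 54 withdrawn, 54 for hut trials, 50 for laboratory bioassays and 80 for other studies. Footnote a says of the 54: "These nets will be tested in hut trials prior to laboratory bioassays and chemical analysis".

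The sample size section states that "a total of 522 ITNs will need to be withdrawn over three years" and, with 70% loss, that 1800 nets will be marked per arm. The statistical analysis section says bioassay data come from "30 nets of each product type sampled at each time point".

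**The concern.** The article prints both a full sampling table and an exact withdrawal total, and neither has room for a trial it describes elsewhere. Field staff who work from Table 1 would collect 54 + 80 = 134 nets per type at 36 months, whereas the design as described calls for 54 + 78 + 80 = 212. The fourth study objective, and the planned model comparing nets washed 20 times with 36-month nets, rest on the missing 78. The 522 is also the figure from which the number of nets to mark was derived, so an error in it carries into that calculation.

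A smaller mismatch sits alongside. The statistical analysis section gives 30 bioassay nets at every time point, while Table 1 gives 50 at 36 months. This changes the denominator of the pass-rate comparison at the final time point.

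**Working it through.** **Inputs**

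- Table 1, nets withdrawn for bioefficacy at 0, 6, 12, 18, 24, 30 and 36 months: 30, 30, 54, 30, 54, 30, 54.
- Table 1, other studies: 80 at each of 12, 24 and 36 months.
- Washed-versus-aged trial: 78 field nets per type.
- Sample size section: 70% loss, 1800 marked per arm.

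**The plan's own figures**

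- Bioefficacy: 30 + 30 + 54 + 30 + 54 + 30 + 54 = 282.
- Other studies: 3 × 80 = 240.
- Total: 282 + 240 = 522, exactly as stated, so the 78 nets are not in it.
- Marking: 522 / 0.30 = 1740. The planned 1800 equals 600 households × 3 nets and yields 1800 × 0.30 = 540, which covers 522 with 18 spare.

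**Adding the second hut trial**

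| Source of the 78 nets | Extra nets | Total | Marked at 70% loss |
|---|---|---|---|
| No reuse | 78 | 522 + 78 = 600 | 600 / 0.30 = 2000 |
| Reuse of the 54 − 50 = 4 uncut nets | 74 | 522 + 74 = 596 | 596 / 0.30 = 1987 |
| Reuse of all 54 before cutting | 78 − 54 = 24 | 522 + 24 = 546 | 546 / 0.30 = 1820 |

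No reuse of the 54 reaches 78. Against the 540 nets that 1800 marked would yield, the plan is 6 short (full reuse) to 60 short (no reuse).

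**How strict that rule is**

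Dividing the total by 0.30 applies the full three-year loss to every withdrawal, including the early ones. Suppose instead that loss is gradual and reaches 70% at 36 months. This is an assumption, since the article gives no loss curve. With S(t) the proportion not yet lost at month t and w(t) the nets withdrawn then:

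nets left before the 36-month withdrawal = 1800 × 0.30 − Σ w(t) × 0.30 / S(t)

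with w = 30, 30, 134, 30, 134, 30 at 0, 6, 12, 18, 24 and 30 months.

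- Constant rate, S(t) = 0.3^(t/36): 540 − (9.0 + 11.0 + 60.1 + 16.4 + 89.7 + 24.5) = about 329, or 338 if the month-0 nets are not drawn from the marked cohort.
- Linear, S(t) = 1 − 0.7t/36: 540 − (9.0 + 10.2 + 52.4 + 13.8 + 75.4 + 21.6) = about 358.
- All loss at the start, S(t) = 0.30: 540 − 388 = 152.

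The need is 212. The first two patterns leave about 117 and 146 nets to spare. The third, which is the protocol's own rule, leaves the plan 60 short.

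**The case against.** - **The nets can probably be found.** A reader might infer that following Table 1 leaves the washed-versus-aged trial without field nets. The documents do not support that: under gradual loss enough marked nets remain, and the section on that trial states the 78 itself, so the team running it has the number. This part stands. The fault lies in the stated allocation and total.
- **The 80 nets for other studies would cover 78.** Numerically they would, but no text assigns them. The study design section lists hut trials and other studies as separate uses, and the same 80 appears at 12 and 24 months, when no such trial is planned.
- **Reuse is not expressly barred.** The one-night limit is written for the annual trials. However, the annual-trial nets are to go to the laboratory immediately after hut testing, and full reuse still leaves 24 missing. The shortfall is therefore a range, and 2000 marked nets is only its upper end.
- **Month 0.** The text lists household sampling from 6 months on. If the 30 month-0 nets are not from the marked cohort, the base is 522 − 30 = 492. With no reuse this gives 570 nets (1900 marked), and with full reuse 516, which 1800 marked would cover. Table 1's title, however, attributes every row to cohort 2, and the 522 includes them. On either reading the 36-month row is still short.
- **Timing.** A reader might also infer that under-withdrawal could not be repaired, or that the 36-month round can still be changed. Neither is established. No text bars a further visit to households. Nets were distributed in 2020 and the article appeared in September 2023, so the 36-month point may already have arrived; the status section reports surveys complete only to 24 months.

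**Conclusion.** The omission is real and follows from the document's own figures. For Interceptor, Interceptor G2 and Royal Guard, the 36-month row is short by 78 nets per type without reuse, 74 with reuse of the uncut nets, and 24 with reuse of all 54. Taking Table 1's rows as printed, the total withdrawal is 546 to 600, not 522. The protocol's loss rule turns this into 1820 to 2000 marked nets against 1800.

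The practical consequence is limited. If loss is gradual, roughly 330 to 360 marked nets per type remain at 36 months against 212 needed, so no extra marking is required. That conclusion rests on the assumed loss pattern.

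PermaNet 3.0 is outside this count because its nets come from another district and not from cohort 2. The 30-versus-50 bioassay mismatch is a separate and minor inconsistency.

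**What to change.** Reconcile Table 1, the section on the washed-versus-aged trial and the sample size section in one of two ways.

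1. Add the 78 nets to the 36-month row, so that hut-trial nets become 54 + 78 = 132, the Table 1 bioefficacy total 282 + 78 = 360 and the overall total 360 + 240 = 600. State why 1800 marked nets still suffice, giving the assumed loss pattern.
2. State explicitly which of the 54 annual-trial nets or the 80 other-studies nets supply the trial, and correct the row and totals to match.

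Letting the 13-treatment trial stand in for the nine-treatment 36-month trial would be a change of design, because the article describes them as separate. It should not be presented as a correction.

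In the statistical analysis section, change the 30 nets to 30 nets (50 at 36 months).

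The cost is a table and text edit, plus replacement nets for at most 78 further withdrawals per type (3 × 78 = 234 over the three types), which the described design already implies.
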